**Table 9-3 Minimum detectable differences in response rates between 2 groups (of size 30)**

| True response rate 1 st group (%) | Minimum detectable response rate 2 nd group (%) |           |
|----------------------------------------------|------------------------------------------------------------|-----------|
|                                              | 80% power                                                  | 90% power |
| 10                                           | 44                                                         | 49        |
| 20                                           | 58                                                         | 63        |
| 30                                           | 69                                                         | 74        |
| 40                                           | 78                                                         | 83        |
| 50                                           | 86                                                         | 90        |
| 60                                           | 93                                                         | 96        |
| 70                                           | 98                                                         | >99       |

An alternative to formal comparisons of groups in Part B is to rank the vaccine groups by their immune response rates. We assess the reliability of this study to select the best group

with respect to the magnitude of their response rates. See Table 9-4 below. Each line in the table shows the results of N=40,000 simulated datasets generated using two (best/ next best) different binomial probabilities for 3 groups of size 30, with the best (highest) response probability used to generate data for one group and the next best response probability used to generate data for the remaining 2 groups. These simulations illustrate the probability of correctly selecting the highest response group 90% (or 80%) of the time [101] given the assumed parameters (best response probability, difference between best and next best).

**Table 9-4 Probability of 90% (80%) correct selection of regimen with highest immunology response (n=30 per group) among 3 groups**

| Next Best response probability (%) | Best response probability (%) | Difference |
|------------------------------------|-------------------------------|------------|
| 10                                 | 26 (21)                       | 16 (11)    |
| 20                                 | 39 (34)                       | 19 (14)    |
| 30                                 | 50 (45)                       | 20 (15)    |
| 40                                 | 61 (55)                       | 21 (15)    |
| 50                                 | 70 (65)                       | 20 (15)    |

## 9.5 Statistical analysis

All data from enrolled participants will be analyzed according to the initial randomization assignment regardless of how many vaccinations they received. Since enrollment is concurrent with receiving the first vaccination, all enrolled participants will have received one vaccination and therefore will provide some safety data. The analysis is intent-to-treat; however, individuals who are randomized but not enrolled do not contribute data and hence are excluded. Because of blinding and the brief length of time between randomization and enrollment—typically no more than 4 working days, according to the HVTN MOP (Study Operations >Enrollment >Randomization)—very few such individuals are expected.

Analyses for primary endpoints will be performed in SAS. All other descriptive and inferential statistical analyses will be performed using SAS, S-Plus, and/or R statistical software.

No formal multiple comparison adjustments will be employed for safety or immunogenicity endpoints that address specified scientific questions (e.g., humoral- and cellular-based endpoints). However, multiple measurements of a specific type of immune response may be treated as a collection of hypotheses that requires a multiplicity adjustment. For example, determination of cellular immune responses to several different HIV-1 peptide pools as measured by the IFN- $\gamma$  ELISpot assay may entail a multiplicity adjustment to account for the multiple peptide pools considered.

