### 9.2 Objectives

The primary objective of this trial concerns safety; the secondary objectives concern immunogenicity and social impacts.

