**Table 9-1 Probability (%) of response for different safety scenarios**

| True event rate (%) | Pr(0/10) | Pr(2+/10) | Pr(0/30) | Pr(2+/30) |
|---------------------|----------|-----------|----------|-----------|
| 1.0                 | 90.4     | 0.4       | 74.0     | 3.6       |
| 3.4                 | 70.0     | 4.6       | 34.3     | 28.3      |
| 5.0                 | 59.9     | 8.6       | 21.5     | 44.6      |
| 10.0                | 34.9     | 26.4      | 4.2      | 81.6      |
| 20.0                | 10.7     | 62.4      | 0.1      | 98.9      |
| 30.0                | 2.8      | 85.1      | <0.1     | >99.9     |
| 40.0                | 0.6      | 95.4      | <0.1     | >99.9     |
| 50.0                | <0.1     | 98.9      | <0.1     | >99.9     |
| 60.0                | <0.1     | 99.8      | <0.1     | >99.9     |

If none of the 130 participants receiving the vaccine experience serious adverse experiences to the vaccine, the exact 95% 2-sided upper confidence bound for the rate of such reactions in the population is 2.8%. Restricted to any of the vaccine arms (n=10) in Part A, the exact 95% 2-sided upper confidence bound for this rate is 31%. Restricted to any of the vaccine arms (n=30) in Part B, the exact 95% 2-sided upper confidence bound for this rate is 12%.

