### 9.5.3 Safety analysis

#### *Reactogenicity*

The number and percentage of participants experiencing each type of reactogenicity sign or symptom will be tabulated by severity and vaccine regimen. For a given sign or symptom, each participant's reactogenicity will be counted once under the maximum severity for all injection visits.

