## 12 Procedures

Participants are considered to be enrolled only upon receipt of the first study vaccination at Day 0.

HVTU and HVTN Laboratory Program staff will conduct pre-enrollment and post-enrollment study procedures according to HVTN procedures as specified in the HVTN MOP (Study Operations). Any procedures which vary from the HVTN standard will be defined in the *HVTN 060 Study Specific Procedures*.

Pre-enrollment and post-enrollment procedures are performed on all participants (unless otherwise noted) at the time points indicated in Appendix B, Appendix C, and Appendix D, using the blood draw volumes specified.

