### 13.3.1 Administration of vaccinations

Syringes should be kept refrigerated at 2° to 8°C (36° to 46°F) until just prior to injection unless the administration is immediately after preparation. Administer the vaccine into the deltoid muscle after preparation of the site with alcohol. The same deltoid should be used at each vaccination visit unless medically contraindicated. If the injection is administered in the opposite deltoid due to a medical contraindication, the appropriate study staff should document this clearly and submit a Study Product Administration Error form. Under this circumstance, this is NOT a protocol violation.

**As significant adverse experiences—including cardiac arrest and death—have occurred with intravascular delivery of bupivacaine, it is essential that aspiration for blood be performed prior to injection of all *gag* DNA, *IL-12* DNA, or their placebo injections to ensure that i.v. delivery does not occur.**

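### Section 9.5 ties the primary safety tables to randomised arm, with no grouping by product received and no denominator for Group 7 participants who actually got the CTL MEP boost

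*Protocol*

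**What the plan says.** Protocol section 9.5 opens with a rule that makes no exception for safety: "All data from enrolled participants will be analyzed according to the initial randomization assignment regardless of how many vaccinations they received". It then names the approach: "The analysis is intent-to-treat; however, individuals who are randomized but not enrolled do not contribute data and hence are excluded". Section 9.2 states that "The primary objective of this trial concerns safety", so the rule reaches the primary endpoint.

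The analysed set is restricted to people who were injected. Section 12 says: "Participants are considered to be enrolled only upon receipt of the first study vaccination at Day 0". Section 9.5 draws the consequence that "all enrolled participants will have received one vaccination and therefore will provide some safety data".

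For reactogenicity, section 9.5.3 says that each type of "reactogenicity sign or symptom will be tabulated by severity and vaccine regimen", with a participant counted once, at the worst grade over all injection visits. Prime and boost are not separated. The adverse experience tables are described by severity and relationship, with no mention of product received.

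Section 9.5.4 states intent-to-treat again, separately, for immunogenicity.

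**The concern.** The usual question for a safety table is what happened to people who were given a product. Section 9.5 answers a different one: what happened to people assigned to it. The two coincide when everyone receives the assigned product and the full series. They part in two situations.

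- **Wrong product given.** Doses are drawn up or mixed at the site, and active and placebo syringes carry a shared label (section 13.2). If the wrong syringe is given, intent-to-treat leaves the resulting events in the assigned column.
- **Boost not given in Group 7.** This arm switches to a different product, CTL MEP with RC529-SE and GM-CSF, at months 6 and 9 only (section 13.1). Its safety as a boost is part of a Part B primary objective (section 6.1). A participant whose vaccinations stop before month 6 never meets that product but remains in the arm's denominator. Sections 14.5.1 and 14.5.2 make this foreseeable: injections outside the window are not allowed, a missed window ends the schedule, and certain related Grade 3 or 4 events end it too. Stops for reactions are not a random subset.

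What is at stake is the accuracy of small-sample rates in the final safety tables of a trial in which, by sections 4.1 and 4.2, neither plasmid has previously been given to humans.

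**Working it through.** **1. The plan's own figures.** Section 9.4.1 gives exact two-sided 95% upper bounds when no event is seen. The formula is 1 − 0.025^(1/n).

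| n | Computed | Printed |
|---|---|---|
| 130 | 2.80% | 2.8% |
| 10 | 30.8% | 31% |
| 30 | 11.6% | 12% |

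The chance of at least one event is 1 − (1 − p)^n: 90.5% for n = 10 at 21%, and 91.8% for n = 30 at 8%, against a stated 90% in each case. All of these reproduce. They describe the enrolled vaccine arms.

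**2. Wrong product.** The documents give no dosing-error rate, so this shows only what one event is worth.

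- Part A vaccine arm: 0/10 against 1/10, a shift of 10 points.
- Part B vaccine arm: 0/30 against 1/30, a shift of 3.3 points.
- Pooled Part B placebo: 0/18 against 1/18, a shift of 5.6 points.

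The direction depends on the error. Two hypothetical cases:

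- A Group 4 placebo recipient is given active product and reacts. By assignment the table reads 0/10 vaccine and 1/2 placebo. By product received it reads 1/11 (9.1%) and 0/1. The active rate is understated.
- A Group 5 participant assigned *gag* DNA alone is given *gag* plus *IL-12* DNA and reacts. By assignment Group 5 shows 1/30 (3.3%). By product received the *gag*-alone column shows 0/29. The *gag*-alone rate is overstated.

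**3. Missed boost in Group 7.** Assume k of the 30 vaccinees never receive CTL MEP, so m = 30 − k are exposed. A reaction that occurs only after the boost, with true rate p, has an expected share of p × m/30 when counted over 30. The zero-event bound for those boosted is 1 − 0.025^(1/m).

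| k (assumed) | m | True 20% shows as | True 8% shows as | Zero-event bound, boosted only |
|---|---|---|---|---|
| 0 | 30 | 20% | 8.0% | 11.6% |
| 3 | 27 | 18% | 7.2% | 12.8% |
| 6 | 24 | 16% | 6.4% | 14.2% |
| 9 | 21 | 14% | 5.6% | 16.1% |

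For k = 6: 0.20 × 24/30 = 0.16, and 1 − 0.025^(1/24) = 0.142.

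Section 9.5.3 plans no booster-specific table. These percentages are what a boost-only reaction would contribute to the Group 7 regimen row. A symptom that also occurs after priming is merged with it at the worst grade, so the boost cannot be read off that row at all.

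**The case against.** The strongest reply is that section 9.5 already describes, in practice, an all-vaccinated set. Its wording concerns how many vaccinations were received, not which product; the wrong-product consequence is inferred from the intent-to-treat label, and no error rate is given. Decisions during the trial do not rest on the final tables: pause rules act on single events (section 14.3), serious events are listed per participant (section 9.5.3), and the Safety Monitoring Board sees unblinded data (section 14.7.4). An as-treated set could be left to an analysis plan. Counting only boosted participants also selects people who tolerated priming.

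Much of this stands, and it rules out several stronger readings that a reader might infer:

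- *That wholly unexposed people dilute every arm.* They do not; enrolment requires the first injection. Only the Group 7 boost product can be missed altogether by someone in its arm.
- *That section 9.4.1 uses a different population.* The sentence beginning "If none of the 130 participants receiving the vaccine experience serious adverse experiences to the vaccine" describes the enrolled vaccine recipients, each with at least one dose. The 14.2% above answers a different question and does not correct the printed 12%.
- *That the bias always understates toxicity.* The Group 5 example runs the other way.
- *That the protocol shows wrong-product errors being captured because "the appropriate study staff should document this clearly and submit a Study Product Administration Error form".* That instruction in section 13.3.1 concerns injection in the opposite deltoid for a medical reason. The dispensing records required by section 13.5 are better support for knowing what was given.

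What does not stand is the appeal to an analysis plan. The protocol fixes the assignment rule itself, for all data. The in-trial safeguards protect participants but do not correct rates or column attribution in the planned tables.

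**Conclusion.** The point holds in a limited form. Section 9.5 binds the primary safety data to randomised assignment and provides no grouping by product received. The consequences are misattribution after a wrong-product injection, in either direction, and a Group 7 denominator that includes anyone never given CTL MEP.

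The likely size is modest. One misplaced event is worth 10 points in a Part A vaccine arm and 3.3 points in a Part B arm. With 10% to 30% of Group 7 unboosted, a true 20% booster reaction rate loses 2 to 6 points, and the zero-event bound for those boosted is 12.8% to 16.1%, against 11.6% for all 30. The missed-boost counts and the true reaction rates are assumptions; the documents supply neither. If nobody misses the boost and no syringe is mistaken, the two groupings agree. No figure in section 9.4.1 needs to change. The point merits action because the endpoint is primary and the remedy is cheap.

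**What to change.** In section 9.5:

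- Keep analysis by randomised assignment for immunogenicity, which section 9.5.4 already states on its own.
- Tabulate reactogenicity, adverse experiences and laboratory safety by product actually received.
- For Group 7, add a table of post-boost events with participants who received CTL MEP as the denominator.
- List every participant whose received product differs from assignment.
- Keep the as-randomised safety table as a supplement.

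The cost is a paragraph of text, a received-product flag in the safety dataset and one added table. Conduct and sample size are untouched. There are two downsides. Safety and immunogenicity denominators may differ. Boost-recipient rates also describe a selected group that tolerated priming, which the retained as-randomised table helps to show.

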### 9.5.1 Analysis variables

The analysis variables consist of baseline variables, safety variables, immunogenicity variables, and social impact variables for primary and secondary objective analyses.

### 9.5.2 Baseline comparability

Groups will be compared for baseline characteristics including demographics and laboratory measurements, using descriptive statistics.

### 9.5.3 Safety analysis

#### *Reactogenicity*

The number and percentage of participants experiencing each type of reactogenicity sign or symptom will be tabulated by severity and vaccine regimen. For a given sign or symptom, each participant's reactogenicity will be counted once under the maximum severity for all injection visits.

#### *Adverse experiences*

Adverse experiences will be analyzed using MedDRA preferred terms. The number and percentage of participants experiencing each specific adverse experience will be tabulated by severity and by relationship to treatment. For the calculations in these tables, each participant's adverse experience will be counted once under the maximum severity or the strongest recorded causal relationship to treatment.

A complete listing of serious adverse experiences for each participant will provide details including severity, relationship to treatment, onset, duration and outcome.

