**Table 14-2 Adverse experience notification and safety pause rules for Part A**

| Toxicity | Symptom/AE                                                                                                                  | HVTU action | SDMC action | Criterion for pause                                                             |
|----------|-----------------------------------------------------------------------------------------------------------------------------|-------------|-------------|---------------------------------------------------------------------------------|
| Grade 4  | Any lab abnormality, local or systemic symptom, or adverse event                                                            | Immediate   | Immediate   | ≥1 vaccine-related symptom at specified grade                                   |
| Grade 3  | Any lab abnormality, local or systemic symptom, or adverse event                                                            | Immediate   | Immediate   | ≥1 vaccine-related symptom at specified grade                                   |
| Grade 2  | Erythema, induration                                                                                                        | Immediate   | Immediate   | ≥1 vaccine-related symptom at specified grade                                   |
| Grade 2  | Lab abnormality, fever, vomiting, other clinical AE (except subjective local and systemic symptoms, erythema or induration) | Prompt      | Prompt      | ≥2 pts experience the same vaccine-related symptom at specified grade or higher |

Immediate: HVTU notifies SDMC Clinical Affairs staff immediately by pager or live phone (not voice mail).

SDMC Clinical Affairs staff notifies PSRT, PAB, RCC/RAB, HVTN SMB, and participating HVTUs as soon as possible that vaccinations are held until further notice.

Prompt: HVTU submits completed forms as soon as possible (and within 1 working day of receiving notice of event). SDMC Clinical Affairs staff notifies PSRT, PAB, RCC/RAB, HVTN SMB, and participating HVTUs as soon as possible during working hours (Pacific Standard Time)—or, if the information was received during off hours, by the morning of the next work day—that vaccinations are held until further notice.

Phone number and pager number are listed in *HVTN 060 Study Specific Procedures*

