#### **14.7.5 Review for dose escalation**

The Protocol Safety Review Team will examine the safety and reactogenicity events for all participants in Groups 1 and 2 combined and Group 3 to date and will discuss every event that triggers the pause rules and determine the advisability of continuing the dose escalation. At a minimum, if 2 or more participants enrolled in a given group report the same Grade 4, vaccine-related reactogenicity or adverse experience, then further vaccinations will be permanently suspended (in that group and any other group at a higher dose level). As noted in the pausing rules (see Section 14.3.1), any such Grade 4 event will require protocol safety review team consultation with the US FDA and HVTN SMB. Additionally, vaccinations may be suspended for any safety concern if, in the judgment of the protocol safety review team, participant safety may be threatened.

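### The adverse experience tables in Section 9.5.3 take worst severity and strongest causality separately, so they do not show how many participants had a vaccine-related event of a given grade

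*Protocol*

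**What the plan says.** Protocol Section 9.5.3, under Adverse experiences, sets the layout: "The number and percentage of participants experiencing each specific adverse experience will be tabulated by severity and by relationship to treatment". It then sets the counting rule: each participant's "adverse experience will be counted once under the maximum severity or the strongest recorded causal relationship to treatment".

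The only place in that section where severity and causality stay attached to the same event is the listing: "A complete listing of serious adverse experiences for each participant will provide details including severity, relationship to treatment, onset, duration and outcome". It covers serious events. The reactogenicity table has severity and regimen but no relationship: "The number and percentage of participants experiencing each type of reactogenicity sign or symptom will be tabulated by severity and vaccine regimen".

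The rules that governed the trial use the two attributes together:
- Table 14-2 pauses Part A on "≥1 vaccine-related symptom at specified grade" for Grades 3 and 4 (and for Grade 2 erythema or induration), and on "≥2 pts experience the same vaccine-related symptom at specified grade or higher" for other Grade 2 findings. Table 14-3 is built the same way for Part B.
- Section 14.5.2 stops a participant's vaccinations for Grade 4 events, and for certain Grade 3 events, once they are confirmed as at least possibly related.
- Section 14.7.5 suspends a group permanently "if 2 or more participants enrolled in a given group report the same Grade 4, vaccine-related reactogenicity or adverse experience".

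**The concern.** Severity and relatedness belong to an event. The counting rule detaches them: it takes the worst grade over all of a participant's episodes of a term, and the strongest causality over all of them, without requiring that both come from one episode. The word 'or' does not settle whether the output is two one-way tables or one crossed table, and neither form is satisfactory.

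Safety is the primary objective, and Sections 4.1 and 4.2 say that the plasmids have not been given to humans before. A reader of the final report will want to know, for each regimen, how many participants had a vaccine-related event at each grade. That is also the kind of event by which the protocol pauses and stops vaccination. The tables as described do not give that number, and the listing supplies it only for serious events, so non-serious related Grade 3 events fall between the two.

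**Working it through.** **Figures in the plan.** The disputed sentence carries no figure. The safety bounds near it, in Section 9.4.1, reproduce. For zero events in n, the exact two-sided 95% upper bound is 1 − 0.025^(1/n):
- n = 10: 30.8% (plan: 31%)
- n = 30: 11.6% (plan: "the exact 95% 2-sided upper confidence bound for this rate is 12", in percent)
- n = 130: 2.8% (plan: 2.8%)

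**What the two tables fix.** For one preferred term in one arm of n participants, let S be the number whose maximum severity is Grade 3 or higher, R the number whose strongest causality is related, and J the number with at least one event that is both. The tables print S and R. All they say about J is that it cannot exceed min(S, R). Its lower limit is 0 whenever S + R ≤ n.
- n = 30, S = 3, R = 3: S + R = 6 ≤ 30, so J is 0 to 3, or 0% to 10%.
- n = 10, S = 2, R = 4: S + R = 6 ≤ 10, so J is 0 to 2, or 0% to 20%.

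**Illustration with assumed data, n = 30, one term.**

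| Data set | Events | At Grade 3 | Related | With a related Grade 3 event |
|---|---|---|---|---|
| A | 3 participants, each with one related Grade 3 event | 3/30 | 3/30 | 3/30 |
| B | 3 participants, each with one unrelated Grade 3 and one related Grade 1 event | 3/30 | 3/30 | 0/30 |

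A and B give identical one-way tables. Counting maximum severity among related events separates them: 3/30 = 10.0% (exact 95% interval 2.1% to 26.5%) for A, and 0/30 (0% to 11.6%) for B.

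**Repeat episodes are not needed.** Give each participant a single event. In C, 3 have a related Grade 3 event and 3 others an unrelated Grade 1 event. In D, 3 have an unrelated Grade 3 event and 3 others a related Grade 1 event. Both print 3 at Grade 3, 3 at Grade 1, 3 related and 3 unrelated, yet J is 3 in C and 0 in D.

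**Crossed reading.** If the two maxima were cross-tabulated, C and D would be shown correctly. The three participants in B would appear as related Grade 3, which none of them had. This error needs two episodes of one term in the same person, discordant in both grade and causality.

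**Comparison within the protocol.** Table 4-1 reports the preceding trial's events that were at least possibly related, split into mild, moderate and severe. It restricts to related events first and grades them second. Section 9.5.3 does not specify this for the present trial.

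**The case against.** The strongest reply is that no pause or stopping decision waits for these tables. Section 14.7.1 has staff screen daily for serious events and events that meet pause criteria, Section 14.7.5 has the safety review team discuss each event that triggers a pause, and Section 14.7.4 gives the monitoring board unblinded comparisons and individual serious-event reports. This stands. A reader might infer that the counting rule weakens the protection of participants during the trial, and the protocol does not support that.

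A reader might also infer that every pause and stopping rule rests on the rate of related severe events. That is too strong in three ways. Several pause criteria act at Grade 2. Some grounds for stopping (pregnancy, HIV infection, a missed window, investigator or review team judgment) use neither attribute. Nearly all the criteria are counts. The one with a percentage, in Table 14-3, concerns subjective symptoms that belong to the reactogenicity table.

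It can further be said that a cross-table may sit in a statistical analysis plan that is not shown, and that most related Grade 3 and 4 events would be known individually from pause records. Both are fair, and nothing in Section 9.5.3 forbids further tables. But the counting rule is written in the protocol, so an analysis plan that follows it would carry it over, and pause records are not a planned summary by regimen. The absence of confidence intervals on safety percentages, and of a listing for all Grade 3 and higher events, can properly be left to the analysis plan and is no error.

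Finally, two one-way tables are the more natural reading, so the mismatched-episode problem is only a possibility. The loss of the joint count remains under that reading.

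**Conclusion.** The point holds in a limited form. As worded, the adverse experience tables do not identify how many participants had a vaccine-related event of a given grade, and the serious-event listing recovers this only for serious events. The uncertainty for a term runs from 0 up to the smaller of the two printed counts: 0% to 10% in the Part B illustration and 0% to 20% in the Part A one. Those counts are assumed. The protocol gives no frequency for terms with both related and unrelated events, so the practical size in this trial is unknown. The consequence is confined to the final description of safety, and real-time monitoring is unaffected. This is a cheap improvement to the primary safety analysis, not a flaw that threatens the trial.

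**What to change.** Reword the counting rule in Section 9.5.3 to define two tables, both by regimen (a factor that the adverse experience sentence does not name):
1. All causes: each participant counted once per preferred term at the maximum severity.
2. Related only: first restrict to events judged possibly, probably or definitely related, then count each participant once per preferred term at the maximum severity among those events. This is the layout of Table 4-1, split by regimen.

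The cost is a sentence of text and one additional table. Severity and relationship are already recorded for adverse experiences, so no new data are needed. Exact intervals for arm-level rates and a listing of all Grade 3 and higher events would be useful companions but are optional.
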